## 4.2 BAMP hypothetical sub-study

We will seek to recruit 148 participants to this sub-study (74 in PIS group and 74 in MMI group). This is to allow for 20% of those randomised not being able to complete the questionnaires (e.g. due to time available or not completing all questionnaires). The questionnaires have 9 Likert scale questions with each of these questions having a score option of 0-4, so the total possible score range is 0-36 (for example 0 means very hard and 4 means very easy; Please see appendix). A difference between groups (MMI versus PIS) of 4.5 (reflecting a mean of 0.5 point different on each of the 9 questions with a Likert scale) would be meaningful. Standard deviation (SD) on the scale of pooled scores is 6.75 (estimated that 95% scores would fall between 4.5 and 31.5 is 27, dividing 27 by 4 for approximate SD = 6.75). Power is 90% and significance level = 0.01. Further information about the questionnaires is given in Section 6.2.3.

# Randomisation

Allocation to groups will be achieved by random number generator or another randomisation method that suits the practicalities of the host trial. Participants will be randomised 1:1 to either PIS or MMI (two arms) in the BAMP sub-study. In FORCE clusters (hospitals) are randomised to either PIS or MMI. Otherwise, participants will be randomised 1:1:1 to one of PIS, MMI or both.

Masking of the allocation at outcome measurement is not possible but also irrelevant: the patient cannot be masked to the information format s/he will receive but, as s/he will be unaware of the embedded information trial, a lack of masking will not affect his/her responses on the self-completion measures, or have any biasing effect on their decisions on trial participation or continuation.

# Outcomes

## 6.1 Primary outcome (Recruitment - MMI only vs PIS only)

The primary outcome is recruitment to each host trial between the MMI only arm and the PIS only arm. For recruitment we will calculate the proportion of patients who agree to participate from the total approached, for each arm of the embedded trial. We will assume that patient eligibility for host trial participation will have been assessed before an approach has been made.

Data on recruitment to the host trial will be recorded automatically within the host trial dataset.

## 6.2 Secondary outcomes

### 6.2.1 Recruitment (MMI & PIS vs PIS only)

The secondary recruitment outcome is recruitment to each host trial between the PIS & MMI arm and the PIS only arm. For recruitment, we will calculate the proportion of patients who agree to participate from the total approached, for each arm of the embedded trial. We will assume that patient eligibility for host trial participation will have been assessed before an approach has been made.

### 6.2.2 Retention

For the retention outcome, we will obtain data on the number and timing of drop outs from each host trial. A single time point specified in the final column in Table 3 will be used in the analyses. Data on trial retention will also be recorded automatically within the host trial dataset.

Table 3 – Summary of retention time points

| Trial | Follow – up time points | Time point for assessing retention |
| --- | --- | --- |
| BALANCE | 16 weeks follow up time point | 16 weeks |
| BAMP | 18 months and 3 years | 18 months |
| CHAMP UK | 6, 12, 18, 24 months (primary outcomes); 5 years post randomisation | 6 months |
| FORCE | 1 day, 3 days, 7 days, 21 days, 6 weeks (eCRF via text msg or telephone) | 6 weeks |
| THERMIC-3 | 3 months | 3 months |
| UKALL | After each course of intensive therapy and 3 monthly whilst on therapy | 3 months |

### 6.2.3 Quality of Decision Making

We will also measure the quality of decision making by potential host trial participants. Children and adolescents will be asked to complete a brief decisional scale, adapted from one used within the REFORM trial (unpublished data; [name], [name], [name], [name], [name]) and drawing conceptually on the SURE (3, 4) and DelibeRATE scales (5). When a parent/carer has been involved in the participation decision, we will also ask them to complete the scale. The scale has been adapted to facilitate completion by young children. We will aim to obtain decision quality scores both from individuals who decide to participate in the host trial and those who decline.

In patients who decide to take part, the children and adolescents and/or parent/carer will be asked to complete the decisional scale once the host trial participation documentation has been completed. In patients who decline participation, they will be asked to complete this measure in the clinic or will have them posted at home or emailed, as appropriate.

The adolescent and parent/family versions of the questionnaire contain the same number of questions, with slight changes in the phrasing of questions. The decisional scale contains 9 Likert questions (with 5 possible answer options) and there are a further 3 questions containing space for free text which give participants the opportunity to give further opinion on their experience. There is also a question detailing who filled in the questionnaire (‘patient’ or ‘parent/carer and patient together’). The younger patient version of the questionnaire is of a similar format. The decisional scale contains 3 Likert questions (each with 5 possible answer options) and the further 3 open ended questions (Please see appendix).

The decisional scales will be scored for both the 3 and 9 question version. Answers to each Likert question will be allocated a value of 0-4. The values for each question will be summed to create an overall score, out of 12 and 36, for the two versions of the scale. Up to three missing responses will be allowed on the 9 question scale. One missing value will be allowed on the 3 question version of the scale. A total score will be calculated by replacing the missing values with the mean score from the completed responses given by the participant. Any scores with more than 3 (adolescent and parent/family version) or more than 1 (younger patient version) will not be scored.

## 6.3 Other important information

In order to assess any potential moderating influences of other variables on the effectiveness of the MMIs, we will aim to obtain data within each host trial of children and adolescents’ age, gender, and deprivation score, according to allocation in the embedded trial and to host trial participation decision.

# Analysis

A CONSORT diagram displaying the flow of participants through each trial will be reported.

All analyses will be conducted in STATA v16 (StataCorp, [name]), or later (to be confirmed in final report), following the principles of intention-to-treat with participant’s outcomes analysed according to their original, randomised group. The following sections relate to the separate analyses of the host trials. Details of the meta-analyses are given in Section 8. Analysis of the primary outcome will be checked by a second statistician after they are conducted. The data relating to the main BAMP study and the BAMP sub-study will be analysed separately. Appropriate model diagnostics will be assessed when models are fitted, including checking normality (for continuous outcomes), checking normality of random effects and checking the homoscedasticity of residuals.

As all the analyses include the PIS only arm, it is important to consider the effect of this on the Type 1 error rate. Here, we will not adjust for multiplicity as we only have a single primary outcome comparison (rather than a co-primary outcome or a primary outcome that is a combination of the multiple comparisons).

## 7.1 Baseline data

All participant baseline data will be summarised descriptively by TRECA trial arm. No formal statistical comparisons will be undertaken. Continuous measures will be reported as means and standard deviations (normality will be checked and if non-normal medians and interquartile ranges will be reported) and categorical data will be reported as counts and percentages. Baseline data for some of the host trials will vary due to different trial data collection, all data that is collected will be reported. The baseline data that will be collected for each trial is given in Table 5 in the Appendix. Baseline data will only be available for participants who are randomised into each trial.

## 7.2 Primary analysis (Recruitment - MMI only vs PIS only)

The proportion of eligible patients entering the trial, which is defined as the number randomised over the number of eligible participants approached will be reported by SWAT trial arm. Recruitment rates will be compared using logistic regression, with TRECA allocation included as covariate in the model. Clustering will be accounted for in the analysis of FORCE, by including the cluster variable as a random effect. The primary comparison is between the MMI only arm and the PIS only arm, hence this pairwise comparison will be extracted from the model. The results from the regression will be presented as odds ratios, with associated 95% confidence intervals and p-values.

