**UKALL**: The UKALL trial is a multicentre, phase III, randomised controlled trial, with two phases of randomisations. The aims are to define whether further refinement of minimal residual disease (MRD) based risk stratification and treatment regimen improves survival whilst reducing overall burden of therapy in children and young adults suffering from acute lymphoblastic leukaemia or lymphoblastic lymphoma.

Table 1 is given below outlining the main characteristics of all the host trials. Table 2 gives the details of the hypothetical study in BAMP. The type of questionnaire are as follows:

- Y = younger patient version
- O = older patient version
- P/F = patient family version

Table 1 – Host trial summary

| Trial | Target Sample Size | Expected TRECA sample size | Type of randomisation in trial | Type of randomisation in TRECA | TRECA arms being used | Decision making questionnaires used |
| --- | --- | --- | --- | --- | --- | --- |
| BALANCE | 66 | 100 | Individual | Individual | PIS, MMI or both | Y, P/F |
| BAMP | 60 | 10 | Individual | Individual | PIS, MMI or both | O, P/F |
| CHAMP-UK | 289 | 413 | Individual | Individual | PIS, MMI or both | Y, P/F |
| FORCE | 696 | 1071 | Individual | Cluster | PIS or MMI | P/F |
| THERMIC-3 | 94 | 118 | Individual | Individual | PIS, MMI or both | Y, O, P/F |
| UKALL | 40 | 50 | Individual | Individual | PIS, MMI or both | Y, O, P/F |

Table 2 – Characteristics of hypothetical BAMP sub-study

| Trial | Target Sample Size | Expected TRECA sample size | Type of randomisation in TRECA | TRECA arms being used | Decision making questionnaires used |
| --- | --- | --- | --- | --- | --- |
| BAMP sub-study | 148 | 148 | Individual | PIS or MMI | O |

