### 7.3.3 Quality of Decision Making

The responses to each question (including the amount of missing responses) and the calculated total scores of the decisional questionnaire will be summarised descriptively overall and broken down by host trial, TRECA allocation and type of questionnaire (younger patient, adolescent or parent/family). A bar chart showing the total scores for each of the three TRECA arms will be included.

As a patient and their parent/carer may both fill in a questionnaire, all the data from the all three questionnaires will not be combined, as all the scores would not be independent. Hence, scores for patients (younger or older) and parents/family questionnaires will be analysed separately using a linear regression, with TRECA allocation and host trial status (whether the participant went on to enter the trial) included as a covariates. Clustering will be accounted for by using the cluster variable as a random effect. Mean difference will be presented with 95% confidence intervals.

If both the younger and older patient questionnaires are used in a host trial the questionnaire data from the younger and older patient questionnaires will be combined. The scores for these will be standardised within the trial by subtracting the sample mean score from the observed score and dividing the result by the sample standard deviation, where the ‘sample’ refers to the subset of participants that have used that questionnaire. Then the standard scores for all participants will be analysed as described above.

To assess the robustness of the method used to replace the missing values, a sensitivity analysis will be conducted, where the analysis will be repeated using only the questionnaires in which all 9 questions were answered.

Both the above analyses (in this section) will be repeated for only the participants who went onto to enter a trial.

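### FORCE is allocated by hospital but its random-intercept analysis has no small-sample method, so its own confidence interval is too narrow unless there are about 40 or more hospitals

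*SAP*

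**What the plan says.** The SAP's Randomisation section states: "In FORCE clusters (hospitals) are randomised to either PIS or MMI". Table 1 in section 2.2 lists FORCE as the only host trial with cluster allocation for TRECA, with 1,071 people expected over two arms.

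For recruitment, section 7.2 fits a logistic regression and adds: "Clustering will be accounted for in the analysis of FORCE, by including the cluster variable as a random effect". It reports an odds ratio with its own 95% interval and p-value for each host trial. Section 7.3.2 uses the same device for retention, with further covariates. Section 7.3.3 uses it in a linear regression of decision scores: "Clustering will be accounted for by using the cluster variable as a random effect". FORCE uses only the parent/family version.

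Sections 8.1 and 8.2 pool the odds ratios, and section 8.3 the mean differences, in random-effects meta-analyses with a fixed-effects sensitivity analysis.

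The SAP names no small-sample correction, degrees-of-freedom rule or reference distribution. The nearest safeguard is the general check, under Analysis, that random effects look normal, which does not address this problem. The number of FORCE hospitals and the intracluster correlation (ICC) are not given.

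**The concern.** When the intervention varies only between hospitals, the precision of its effect depends heavily on how well the between-hospital variance is estimated. With few hospitals, maximum likelihood tends to underestimate that variance, and a normal-based interval ignores the uncertainty in it. The interval is then too short and the p-value too small.

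FORCE is where this matters most. It is the largest host trial, its result is reported in its own right, and section 2.2 says it was limited to two arms to gain power and allow a sturdier evaluation. Its standard error also sets its weight in the meta-analyses.

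**Working it through.** **Inputs.** From Table 1 (expected TRECA samples): FORCE 1,071; BALANCE 100; BAMP 10; CHAMP-UK 413; THERMIC-3 118; UKALL 50. The last five randomise 1:1:1, so two thirds enter the primary comparison. Assumed, because the SAP does not give them: 6 to 50 hospitals, ICC 0.01 to 0.10, and a normal reference distribution. Recruitment of 65% follows from Table 1 (696/1,071). The plan has no figure of its own to reproduce here: the sample size in section 4.1 contains no design effect.

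**1. Head count.** 100 + 10 + 413 + 118 + 50 = 691; 691 x 2/3 = 461; 1,071/(1,071 + 461) = 1,071/1,532 = 69.9%.

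**2. Type I error of the normal-based test, nominal 5%.** These are three simulations of FORCE under no effect, fitted with the random-intercept logistic model. A: unequal hospitals, latent-scale ICC 0.02-0.10, 700 runs per cell. B: equal hospitals, ICC 0.01-0.10, 1,000 runs. C: unequal hospitals, 500 runs. The last column is B with t on hospitals minus 2 degrees of freedom.

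| Hospitals | A | B | C | B with t |
| --- | --- | --- | --- | --- |
| 6 | - | 13.5-17.8% | - | 3.9-7.7% |
| 10 | 10-14% | 9.6-12.8% | 11-17% | 5.1-7.6% |
| 16 | 9-11% | 7.7-8.7% | 10-12% | 5.1-6.6% |
| 20 | - | 6.1-7.8% | - | 4.3-6.2% |
| 24 | 7-9% | - | 7-8% | - |
| 30 | 7-8% | 5.4-8.1% | 7-8% | 4.8-6.8% |
| 40 | - | - | 5-7% | - |
| 50 | - | 6.2-6.7% | - | 5.4-6.2% |

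Simulation error is about 1 point. A hospital-level t-test held 4-6% in A and in C.

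**3. Coverage and standard error.** With an odds ratio of 1.2 and ICC 0.03 and 0.08, coverage of the 95% interval was 88-90% (10 hospitals), 91-92% (16) and 93% (24). The mean model standard error was 85-95% of the true SD. The hospital-level t interval covered 95-96%. In B at 10 hospitals and ICC 0.05, the model standard error was 0.268 against a true SD of 0.304 (88%).

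**4. Pooling weight.** Design effect = 1 + (m - 1) x ICC, with m = 1,071/hospitals. Effective n = 1,071/design effect. With no between-trial variance and a similar variance per person in every trial, FORCE's weight is effective n/(effective n + 461). If its variance is understated by the factor (k - 2)/k for k hospitals, effective n is inflated by k/(k - 2).

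| Hospitals, ICC | Design effect | Effective n | Weight | Weight if understated |
| --- | --- | --- | --- | --- |
| 10, 0.01 | 2.06 | 520 | 53.0% | 58.5% |
| 10, 0.05 | 6.3 | 170 | 26.9% | 31.6% |
| 20, 0.05 | 3.63 | 295 | 39.1% | 41.6% |
| 30, 0.05 | 2.74 | 392 | 45.9% | 47.7% |

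The excess weight is about 2 to 6 points. It is 5-10 points at 6 hospitals and about 1 at 50.

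**5. Pooled test.** The section 8.1 pooling was simulated with Table 1 sizes, odds ratio 1, ICC 0.02-0.10, a normal approximation and 3,000 runs per cell. It assumed the DerSimonian-Laird method and no true between-trial variance. Type I error of the random-effects test was 6-8% at 6 hospitals, 5-6% at 10, about 4.5% at 16 and 4-6% at 24-50. The fixed-effects test gave 8-10% at 10 hospitals and about 6-8% at 16 or more. A hospital-level standard error for FORCE still left 7-8% at 10.

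**The case against.** The best defence has three parts. First, the SAP does recognise the clustering, and the random intercept already reduces FORCE's influence. Secondly, a hospital count is detail that a protocol commonly carries, and the SAP refers to its protocol for full design details; with 40 to 50 hospitals little is lost. Thirdly, section 4.1 looks to the meta-analysis for the robust answer, and step 5 shows the pooled random-effects test close to nominal at 10 or more hospitals.

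Much of this stands, and it rules out stronger readings that a reader might infer:

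- That FORCE has few hospitals and its interval is therefore certainly too narrow. The SAP says only that the trial is multi-centre, so the error is conditional.
- That FORCE carries 70% of the pooled estimate. That figure counts people; the weights in step 4 are well below it.
- That only the number of hospitals carries information. Both counts matter: at 30 hospitals and ICC 0.02 the design effect is 1 + 34.7 x 0.02 = 1.69, an effective n of about 630.
- That the primary pooled conclusion is unsafe. Step 5 does not support this at 10 or more hospitals, although true between-trial variance was not simulated.

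The objection does not remove the gap itself. A hospital count in the protocol would not supply an inference method, and that choice belongs in the SAP. FORCE's interval and p-value are reported in their own right.

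**Conclusion.** The point holds conditionally. The plan allocates FORCE by hospital and prespecifies no small-sample method for any of its three outcomes. For recruitment, the inflation of type I error is material at about 6 to 16 hospitals, modest at 20 to 30 and slight from about 40. The consequences are mainly for FORCE's own interval and p-value and for the fixed-effects sensitivity analysis.

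This rests on an assumed ICC of 0.01 to 0.10, 65% recruitment and a normal reference distribution, which the SAP does not state. It also does not say whether the linear model uses maximum likelihood or REML. The simulations concern recruitment; the same reasoning carries over to retention and the parent/family score, but no sizes were computed for those.

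**What to change.** State the number of FORCE hospitals and record the following in the SAP amendment log.

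- **Recruitment (7.2):** analyse hospital-level log odds, with a 0.5 continuity correction, by t on hospitals minus 2 degrees of freedom. At the least, apply that t reference to the planned model, which corrects most but not all of the inflation when hospitals are few.
- **Retention (7.3.2):** keep the planned covariate-adjusted random-intercept model, with a t reference on between-hospital degrees of freedom. Hospital-level log odds are unsuitable here. They are undefined where everyone is retained, and a two-sample t-test would drop the covariates. With 696 randomised in equal hospitals and an assumed 95% retention, the expected number of such hospitals is 16 x 0.95^43.5 = 1.7 of 16, or 30 x 0.95^23.2 = 9.1 of 30. Hospital should enter only as the random effect: Table 4 lists centre as a FORCE stratification factor, and as a fixed covariate it would be aliased with the TRECA allocation.
- **Parent/family score (7.3.3):** fit by REML with Kenward-Roger degrees of freedom.
- **Section 8:** carry the corrected standard error forward where the method yields one. A t reference alone widens FORCE's interval but leaves its weight unchanged.
- **Sensitivity:** report the uncorrected random-intercept result alongside.

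The cost is SAP wording and a modest amount of code. The t critical value exceeds the normal one by 18% at 10 hospitals, 7% at 20 and 4.5% at 30. The unweighted hospital-level estimate had an SD about 1-8% larger in simulation.

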## 7.3 Secondary analyses

### 7.3.1 Recruitment (MMI & PIS vs PIS only)

The secondary outcome is looking at the effect of the addition of MMI to PIS. This pairwise comparison will be extracted from the same model as was used for the primary analysis. This outcome is not applicable for FORCE as they only used the MMI and PIS arms.

### 7.3.2 Retention

The time point for assessing in each trial is given in Table 3. The proportion of the participants who are retained at the specified time point will be reported. This is defined as the number of participants who have reached that time point, over the number of participants randomised into the trial.

The retention rate will be compared using logistic regression, for each host trial, with host trial allocation and TRECA allocation included as covariates. Where a host trial has used stratification variables (see Table 4) in the randomisation, these will be included as covariates in the model. Clustering will be accounted for in the analysis of FORCE, by including the cluster variable as a random effect. Similarly to the recruitment analyses, two pairwise comparisons will be used: MMI only vs PIS only and MMI & PIS vs PIS only. The results will be presented as odds ratios, with associated 95% confidence intervals, and p-values.

Table 4 – Summary of stratification factors

| Trial | Stratification factors |
| --- | --- |
| BALANCE | Type of amblyopia & centre by stratification |
| BAMP | Gender by stratification |
| CHAMP UK | Centre, ethnicity, severity of myopia. The unit of randomisation will be the participant (not the eye) using a minimisation algorithm |
| FORCE | Age & centre by stratification |
| THERMIC-3 | Risk Adjustment for Congenital Heart Surgery (RACH scores) by stratification |
| UKALL | Cytogenetic risk and Minimal residual disease (MRD) level, National Cancer Institute (NCI) Risk, early morphologic response by stratification |

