## 2.2 Host Trials

Host trials may use individual or cluster randomisation as deemed practical and appropriate. Although the trials contains three arms, the two arms of PIS only and MMI only are the main area of scientific interest. We added the third (combined) arm as an option in case host trials or the relevant REC was concerned about ‘MMI only’ being used in recruitment.

Further information is given about each of the individual trials below, and a summary of the characteristics of each trial are given in Table 1 and Table 2. As this study looks at all those approached to enter each trial, the number of participants included in TRECA is expected to be higher than the expected sample size, as seen in Table 1.

**BALANCE**: A trial recruiting children with “Lazy eye" (amblyopia) from 3 sites (2 clinics at Moorfields Eye Hospital in London and 1 clinic in Bedfordshire). In this pilot trial, children will receive, at random, either a Nintendo 3DSXL console with movies, or standard patching/blurring eye-drop treatment.

**BAMP**: A single-centre clinical trial assessing the effectiveness of manipulate surgical treatment to bring the upper jaw forwards in 11-14 years old children. BAMP also contains a hypothetical sub study, where participants will be given information about the trial and they will then be asked if they would hypothetically enter the trial. Due to the fact that this is a hypothetical study and hence different in nature to the other host trials, the results from the sub-study will not be included in the meta-analysis. TRECA materials will be used in both recruitment to the main study and the additional hypothetical sub- study.

**CHAMP UK**: A multicentre trial placebo controlled randomised trial which investigates low-dose atropine eye drops to reduce progression of myopia in children.

**FORCE**: A multi-centre prospective randomised trial of a soft bandage and immediate discharge versus current treatment with rigid immobilisation for acute torus fractures of the distal radius in children. For the FORCE trial, cluster randomisation (by recruitment site) is used for the TRECA allocations. We will use only two arms of TRECA (PIS only versus MMI only) to enable the power to be increased and the impact of the MMIs to be more robustly evaluated.

**THERMIC-3**: A multi-centre trial which considers intermittent antegrade warm blood versus cold blood cardioplegia in children undergoing open heart surgery.

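### FORCE retention model: adjusting for centre makes the TRECA effect non-identifiable, because TRECA allocation was randomised by hospital

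*SAP*

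**What the plan says.** SAP Section 7.3.2 specifies a logistic regression of retention for each host trial, "with host trial allocation and TRECA allocation included as covariates". It then adds a general rule: "Where a host trial has used stratification variables (see Table 4) in the randomisation, these will be included as covariates in the model". For FORCE, Table 4 gives "Age & centre by stratification". The sentence after the rule reads: "Clustering will be accounted for in the analysis of FORCE, by including the cluster variable as a random effect".

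Two other sections fix the unit of TRECA randomisation. Section 2.2 says: "For the FORCE trial, cluster randomisation (by recruitment site) is used for the TRECA allocations". Section 5 (Randomisation) says: "In FORCE clusters (hospitals) are randomised to either PIS or MMI". Table 1 agrees: host-trial randomisation in FORCE is individual, and TRECA randomisation is by cluster.

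Section 8.2 pools the resulting odds ratios in random-effects meta-analyses. Nothing in Section 7.3.2 or 8.2 exempts FORCE from the stratification-variable rule or says that the random effect stands in place of the centre covariate.

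**The concern.** The stratification rule is ordinary practice where the allocation being studied varies within strata. That holds for the FORCE treatment allocation, which is individual. It does not hold for the TRECA allocation in FORCE, which is fixed within each hospital. Centre indicators absorb every difference between hospitals, and the TRECA contrast is entirely a difference between hospitals, so nothing is left from which to estimate it.

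The practical risk is that the failure could pass unnoticed. Software that removes a redundant column may remove a centre indicator rather than the TRECA term. It then prints an odds ratio, interval and p-value labelled as the TRECA effect. That figure would go into the forest plot from the largest of the six host trials.

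**Working it through.** The SAP attaches no figure to the retention model, so there is none to reproduce.

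**1. Algebra.** Write the linear predictor for a participant in hospital k as α_k + β·t_k + (host allocation) + (age), where t_k is 1 for MMI hospitals and 0 for PIS hospitals. Because t_k depends only on k, adding any δ to β and subtracting δ from α_k in every MMI hospital leaves every fitted probability unchanged. The likelihood therefore cannot determine β. A mean-zero hospital random effect is added to the same predictor and its distribution does not involve t_k, so the argument is unaltered.

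**2. Rank check.** N = 696 (FORCE target, Table 1). Columns are intercept, host allocation, age (two levels), TRECA allocation and centre indicators less one. The SAP does not give the number of hospitals, so a range is assumed.

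| Hospitals (assumed) | Columns | Rank | Rank without TRECA |
|---|---|---|---|
| 10 | 13 | 12 | 12 |
| 20 | 23 | 22 | 22 |
| 24 | 27 | 26 | 26 |
| 40 | 43 | 42 | 42 |

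Adding TRECA never raises the rank. With the centre indicators removed, the fixed part has 4 columns and rank 4.

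**3. What would be printed.** One data set was simulated with 20 hospitals and a true TRECA odds ratio of 1. Ordinary logistic models with centre indicators were fitted, dropping one PIS and one MMI hospital indicator in every combination. The TRECA odds ratio ran from 0.16 to 55.1, with the same log-likelihood throughout. Each value is simply the contrast between the two dropped hospitals. On the same data, a clustered model without centre indicators (GEE, exchangeable correlation) gave a single odds ratio of 1.39, with a standard error of 0.34 on the log scale.

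**4. FORCE's share of participants.** Section 7.3.2 sets the retention denominator as the count retained "over the number of participants randomised into the trial", so Table 1 target sizes apply: 66 + 60 + 289 + 696 + 94 + 40 = 1,245. FORCE has two arms. The other trials randomise 1:1:1, so two-thirds of each enters MMI only versus PIS only.

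- All targets met: the other trials give 549 × 2/3 = 366, and 696 / (696 + 366) = 65.5%.
- BAMP at its expected TRECA number of 10 instead of 60: 499 × 2/3 = 332.7, and 696 / 1,028.7 = 67.7%.

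**5. FORCE's weight.** Variance of each log odds ratio = 2 / [n·r(1−r)] + τ², where n is the number per arm and r is retention. For FORCE, n = 348 / [1 + (m−1)·ICC] with m = 696 / number of hospitals. The SAP gives no hospital number, ICC, retention rate or τ², so these are assumptions. Weights with τ² = 0 are below; the two values in a cell are BAMP at 60 and at 10.

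| ICC | 20 hospitals | 40 hospitals |
|---|---|---|
| 0 | 65.5%, 67.7% | 65.5%, 67.7% |
| 0.01 | 58.7%, 61.0% | 62.0%, 64.3% |
| 0.05 | 41.4%, 43.7% | 51.1%, 53.5% |
| 0.10 | 30.3%, 32.3% | 41.9%, 44.2% |

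Example: with 20 hospitals and ICC 0.05, the design effect is 1 + 33.8 × 0.05 = 2.69 and n = 348 / 2.69 = 129.4. The other trials sum to 549 / 3 = 183 per arm, so the weight is 129.4 / 312.4 = 41.4%.

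Adding τ² of 0.05 or 0.2, with retention of 80% or 90%, lowers the weight further. The smallest value is 25.7% (20 hospitals, ICC 0.10, τ² 0.2, retention 80%, BAMP at 60).

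**The case against.** The best defence is that the FORCE sentence is the more specific one. It says how the cluster enters, and the cluster is the hospital, so a sensible statistician would let the random effect carry centre and keep only age as a fixed stratification covariate. On that reading the model is sound and the problem disappears. This is plausible and may be what the authors meant. But the text states the covariate rule without exception and then adds the random effect; it does not say that one replaces the other. By contrast, Section 7.2 uses the same random-effect sentence with no stratification covariates, and so has no such conflict.

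It is also fair to say that retention is secondary and that a dropped-variable message would probably appear when the model is fitted. Both points lower the severity. Neither tells the analyst which column should go.

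A reader might extend the point to the small host trials, where several stratification factors and arms without drop-outs could also upset the model. That is a different problem, and its size cannot be established here because the SAP gives no retention rate. For UKALL, with 40/3 per arm, the chance that at least one of two arms has no drop-out is 1 − (1 − r^(40/3))². That is about 75% at 95% retention, 43% at 90% and 10% at 80%. For BAMP, the figure of 10 counts people expected to be approached, not people randomised. The point is therefore confined to FORCE.

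**Conclusion.** The concern holds for the model as written. With centre as a fixed covariate, the FORCE retention odds ratio for TRECA allocation is not identifiable, whatever the number of hospitals or the retention rate. This assumes that the centre in Table 4 is the same unit as the hospital or recruitment site randomised in TRECA, which is how Sections 2.2 and 5 read.

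The reach is limited. Three wider inferences are not supported:

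- **That the primary result is compromised.** The recruitment model in Section 7.2 contains no stratification covariates, so it is unaffected.
- **That all retention pooling is affected.** FORCE has no combined arm and cannot enter the MMI & PIS versus PIS only pooling. In BALANCE and CHAMP UK, which also stratify by centre, TRECA allocation is individual and the problem does not arise.
- **That FORCE necessarily dominates the pooled estimate.** It supplies about 66-68% of expected participants in the MMI only versus PIS only comparison, but its weight is about 26-68% over the assumed ranges. It outweighs CHAMP UK, the next largest, only while its design effect is below about 348 / 96.3 = 3.6. With τ² of zero or more, that means an ICC below about 0.08 with 20 hospitals or 0.16 with 40.

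Even at the low end, a quarter of one secondary meta-analysis would rest on an arbitrary figure.

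**What to change.** Add one sentence to Section 7.3.2 after the stratification rule: in FORCE, centre is not included as a fixed covariate and enters only as the random cluster effect; the fixed covariates are TRECA allocation, host trial allocation and age. A matching note against FORCE in Table 4 would prevent misreading.

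This makes the fixed part full rank and keeps the adjustment for clustering already planned. It needs no new data and no change to Section 8.2, only an entry in the SAP amendment log.
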